#### Secondary analysis

The analyses for the secondary endpoints will be performed in a similar way to those previously described. The same applies to the secondary endpoint criteria: pain, functional status by WOMAC, maximal walking speed and performance, measurement of peak torques. The comparison of the qualitative parameters (for example the WOMAC scale categorized, for example, by median or quartiles) between the two groups will be made using the Chi-square test or Fisher's exact test (if appropriate).

In order to measure the progression of the different parameters collected during the three visits (mobility, amyotrophy, deformation, effusion, and pain on palpation), we will conduct a longitudinal analysis of the data in two stages by ANOVA for repeated data followed by a post-hoc Tukey-Kramer test and using mixed models (or random effects models) [19] that will allow the measurement of the intrasubject correlation by taking into account the effects of the subject and time (‘random intercept’ and ‘slope’ effects). An associated measurement of the coefficients of intraclass correlation will also be performed. The impact of covariables will be also explored.

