### Objectives and endpoints

The primary objective of this study will be to assess whether eccentric isokinetic strengthening improves the isokinetic strength of the quadriceps more than concentric isokinetic strengthening in patients with medial femorotibial knee osteoarthritis. The concentric isokinetic torque of the quadriceps will be used as primary outcome measure because of its better reliability and reproducibility compared to an eccentric isokinetic torque [15].

The secondary objectives will be to compare the effects of concentric and eccentric isokinetic training on:

1. Static postural balance on a Fusyo™ force platform

2. Temporospatial gait parameters assessed by Gaitrite™

3. Maximal 10 meters and 200 meters at walking speed

4. Range of knee motion

5. Pain, stiffness and function assessed by the Western Ontario and MacMaster Universities osteoarthritis index (WOMAC) questionnaire.

These access joint mobility but also physical function in daily living activities, which influence improved feeling for the most patients. The effects of 6 weeks of training on these parameters will be evaluated after the 12 strengthening sessions and at 6 months. The possible adverse effects of the different strengthening modes will also be analyzed (muscular and articular pain evaluation before and after each session, maximal cardiac frequency during sessions, and muscular lesions).

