### Statistical considerations

#### Justification of the number of subjects to be included

The principal objective of this study lies in the assessment of the increase in the quadriceps isokinetic peak torque of the treated knee as measured using a Cybex Norm™ computerized dynamometer, with the concentric mode, at a speed of 60/second after treatment.

The estimation of sample size was determined on the basis of a greater improvement of muscular strength in the quadriceps of the treated knee (muscular strengthening in the medical treatment of the femorotibial knee osteoarthritis) in the eccentric group compared to the concentric group. From the work of Tüzun *et al.*[10] and Huang *et al*. [9], we learned about the increase in muscular strength of the quadriceps using isokinetic concentric training. The difference between the two groups was estimated at 15% (treated as quantitative) and the standard deviation was fixed at 20 (supposedly identical in the two groups). Also, for a type I error α and a statistical power fixed respectively at 5% (in a two-sided situation) and 90%, 40 patients per group need to be recruited. The rate of ‘lost to view’ for the measurement of the principal endpoint criterion at 6 weeks is considered negligible [10].

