#### Principal analysis

The principal endpoint criterion is the improvement at 6 weeks of treatment of the isokinetic concentric quadriceps peak torque at the speed of 60°/s. The comparison between the randomized groups will be performed using the Student test or the Mann and Whitney test (if the conditions for validity of the Student test are not respected). The comparison between the treatment groups will be performed systematically: 1) without adjustment and, 2) by adjusting other factors whose repartition could be, despite the randomization, unbalanced between the treatment groups.

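### WOMAC is planned both as a score and, optionally, cut at the median or quartiles, without saying which comparison counts; the cut version is the weaker test

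*Protocol article*

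**What the plan says.** All references are to the protocol article.

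- **Objectives and endpoints** lists five secondary objectives without ranking them. The fifth is "Pain, stiffness and function assessed by the Western Ontario and MacMaster Universities osteoarthritis index (WOMAC) questionnaire". Effects are to be evaluated after the 12 sessions and at 6 months.
- **Principal analysis** says the group comparison "will be performed using the Student test or the Mann and Whitney test", the latter when the conditions for the former fail, both unadjusted and adjusted.
- **Secondary analysis** extends this approach to the secondary endpoints: "The same applies to the secondary endpoint criteria: pain, functional status by WOMAC, maximal walking speed and performance, measurement of peak torques". WOMAC is therefore first compared as a score.
- The next sentence of **Secondary analysis** turns to qualitative parameters. Its example is "the WOMAC scale categorized, for example, by median or quartiles", and the comparison "will be made using the Chi-square test or Fisher's exact test (if appropriate").

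No numeric cut-point is given, the choice between median and quartiles is left open, and neither WOMAC analysis is given precedence.

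**The concern.** WOMAC is described in its own section as a 24-item instrument covering pain, stiffness and physical function. It becomes qualitative only if someone cuts it, and cutting it at a median or at quartiles has three drawbacks:

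1. It discards information. A Chi-square test across quartiles also ignores their order.
2. A median or quartile is relative to whatever distribution supplies it, and the article attaches no clinical meaning to it.
3. It adds competing results for the same endpoint, with nothing to say which is the answer.

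The trial's rationale is functional, and WOMAC bears directly on whether a strength gain reaches daily function. If the categorized result were reported in place of the score, a real difference would be easier to miss. If whichever result looked best were reported, a chance difference would be easier to claim.

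**Working it through.** **Inputs.** From Justification of the number of subjects to be included: "The difference between the two groups was estimated at 15% (treated as quantitative"), "the standard deviation was fixed at 20 (supposedly identical in the two groups"), and error rates "fixed respectively at 5% (in a two-sided situation) and 90%, 40 patients per group need to be recruited". These belong to the torque endpoint. The article gives no effect size or SD for WOMAC, so the standardized effect d is an assumption here and is shown over a range. Scores are taken as normal and without ties.

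**Step 1: reproduce the plan's own figure.** d = 15/20 = 0.75.
- Normal approximation: n = 2 × (1.960 + 1.282)² / 0.75² = 37.4, so 38 per group.
- Exact t-test: 38.3, so 39.
- Mann-Whitney (efficiency 3/π): 38.3 / 0.955 = 40.2.
- t-test power at 40 per group: 91%.

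The stated 40 per group is reproduced within 2 patients.

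**Step 2: efficiency of a median split.** Relative to the t-test under normality it is 2/π = 0.637, a loss of 36%. If the split replaced the score, that would equal losing 80 × (1 − 0.637) ≈ 29 of 80 patients.

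**Step 3: efficiency of quartiles with an unordered Chi-square.**
- Grouping alone: Σ(φ(lower cut) − φ(upper cut))² / 0.25 over the four cells = 0.861, a loss of 14%.
- Spending 3 degrees of freedom instead of 1: the ratio of noncentralities needed is 7.849/10.903 = 0.720 at 80% power and 10.507/14.171 = 0.741 at 90% power.
- Combined: 0.861 × 0.720 = 0.62 and 0.861 × 0.741 = 0.64.

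The loss is 36% to 38%, about the same as for the median split, but most of it comes from ignoring the order.

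**Step 4: power by formula, t-test against median split, 40 per arm.** With the cut midway between the arms, p₁ = Φ(d/2) and p₂ = 1 − p₁. Power = Φ{[(p₁ − p₂)√40 − 1.96√(2 × 0.5 × 0.5)] / √(p₁(1 − p₁) + p₂(1 − p₂))}. For d = 0.5, p₁ = 0.599, p₂ = 0.401, and power = Φ[(1.249 − 1.386)/0.693] = 42%.

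| d (assumed) | t-test | median split |
|---|---|---|
| 0.30 | 26% | 18% |
| 0.50 | 60% | 42% |
| 0.65 | 82% | 63% |
| 0.75 | 91% | 75% |

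Patients per arm for 90% power: 86 against 133 at d = 0.50, and 39 against 60 at d = 0.75.

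**Step 5: simulation.** 10,000 trials per scenario, 40 per arm, cut-points from the pooled sample. Each entry is the percentage of trials with p < 0.05.

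| d | t-test | median | quartiles | better of median and quartiles | best of all three |
|---|---|---|---|---|---|
| 0 | 5.0 | 4.2 | 4.5 | 7.2 | 9.8 |
| 0.50 | 60 | 41 | 36 | 48 | 64 |
| 0.75 | 91 | 74 | 71 | 81 | 92 |

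For the median split, Fisher's exact test gave the same rejection rates as Chi-square. The d = 0 row is for one score at one visit. WOMAC has three parts and two follow-up times, so there is more room for selection than this row shows.

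**The case against.** The strongest reply is that the continuous comparison is already planned in the preceding sentence. An added analysis takes nothing away from it. The categorized version is also a doubly hedged illustration of which test suits categorical data, not a commitment. This stands, and it limits the point: the power loss applies only to the categorized analysis, or if that analysis is reported instead of the score.

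It can also be said that cut-points and precedence among secondary analyses usually sit in the full protocol or SAP, neither of which is at hand. That is fair, and the missing cut-points are not the complaint. The complaint is that the article names a weaker method for an endpoint that already has a better one.

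A reader might infer more than the text supports:

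- **That letting the data set the cut-point inflates the type I error.** A pooled cut is blind to arm, and each test alone stays below 5% (4.2% and 4.5%). Only choosing among analyses raises the rate. The article also does not state that the cut comes from the trial sample, although it cites no external one.
- **That the cut ignores baseline or shifts between visits.** The article does not say so. Categorizing the change from baseline would be equally compatible with its wording.
- **That WOMAC is the main patient-important outcome.** It is one of five unranked secondary objectives.

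**Conclusion.** The point holds as a minor correction to a secondary endpoint. The article offers a categorized WOMAC test beside the score comparison and does not say which counts. The categorized tests have about 64% of the t-test's efficiency, which costs roughly 17 to 24 percentage points of power at 40 per arm for d between 0.5 and 0.75. Free choice among the three tests would roughly double the nominal 5% error for a single WOMAC score at a single visit.

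These sizes rest on normal scores without ties and on assumed effects. Skewed or floor-limited WOMAC scores would change them. It would go too far to say that the plan discards a third of the WOMAC information or makes a false negative likely, because the score comparison remains planned. Nothing here touches the primary torque analysis.

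**What to change.** In Secondary analysis:

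1. Delete the median/quartile WOMAC example.
2. State that the between-group WOMAC analysis uses the continuous score adjusted for its baseline value, at 6 weeks and at 6 months.
3. Reserve Chi-square and Fisher for variables that are truly categorical.
4. If a categorized WOMAC summary is still wanted, fix one threshold before unblinding and label the summary as descriptive.

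The cost is analysis wording only. Recruitment does not change. The adjusted model needs a WOMAC score at inclusion, which any assessment of the effect of training already requires.

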#### Clinical examination at inclusion

The following data will be recorded:

1. Knee medical history;

2. Range of motion of the knee;

3. Thigh circumference at 5, 10 and 15 cm from the base of the patella;

4. Blood pressure,

5. Heart rate;

6. Anthropometric measurements (height, weight, body mass index); and

7. Electrocardiogram.

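### The only longitudinal model described names no arm or arm-by-visit term and omits most secondary endpoints, so the 6-month comparison of training modes sits outside it

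*Protocol article*

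**What the plan says.** Objectives and endpoints makes the secondary objectives comparative between the two training modes. They cover balance, gait, walking speed over 10 m and 200 m, range of knee motion, and WOMAC. On timing it states: "The effects of 6 weeks of training on these parameters will be evaluated after the 12 strengthening sessions and at 6 months".

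Secondary analysis contains two separate pieces.

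- The secondary endpoints are to be analysed like the primary one. Under Principal analysis that means a Student or Mann-Whitney comparison of the randomized groups, with and without adjustment. Categorized variables get a Chi-square or Fisher test between the groups.
- A longitudinal analysis is meant to describe progression over three visits. Its variables are "mobility, amyotrophy, deformation, effusion, and pain on palpation". It uses "ANOVA for repeated data followed by a post-hoc Tukey-Kramer test", and then mixed models that measure the correlation within patients "by taking into account the effects of the subject and time", with a random intercept and slope. Covariables are to be explored.

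The section on missing data addresses missing 6-month values as a problem of the longitudinal data. The sample-size section calls loss to follow-up negligible at 6 weeks and gives no rate for 6 months.

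**The concern.** A model with patient and time effects describes how patients change, averaged over both arms. Both arms are trained and the Discussion expects both to gain, so a time effect is likely whichever mode is better. The trial's question is whether the modes differ, and that needs an arm term at each visit.

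The 6-month comparison is the most exposed. By then some patients may be missing, and the longitudinal model is the natural tool because it can use a patient's 6-week value when the 6-month value is absent. As described, that model carries neither the arm contrast nor most of the endpoints of interest. The two-sample tests carry both, but no 6-month time point is stated for them and no missing-data method is tied to them.

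**Working it through.** **1. The plan's own figure.** Inputs from the sample-size section are a difference of 15 ("The difference between the two groups was estimated at 15% (treated as quantitative"), an SD of 20 ("the standard deviation was fixed at 20 (supposedly identical in the two groups"), and error rates "fixed respectively at 5% (in a two-sided situation) and 90%, 40 patients per group need to be recruited".

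- Normal approximation: n = 2 × (1.960 + 1.282)² × (20/15)² = 37.4, so 38 per arm.
- Noncentral t: 39 per arm (power 0.905).
- Allowing for the Mann-Whitney efficiency 3/π: 38 / 0.955 = 39.8, so 40.

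The stated 40 reproduces, with power 0.912 (t) to 0.918 (normal). Nothing below changes it.

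**2. Endpoints against analyses.**

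| Variable | Listed secondary objective | Named for the two-sample tests | In the longitudinal list |
|---|---|---|---|
| Static balance | yes | not by name | no |
| Gait parameters | yes | not by name | no |
| 10 m and 200 m speed | yes | yes | no |
| Range of knee motion | yes | not by name | yes, if mobility means this |
| WOMAC | yes | yes | no |
| Peak torques | no | yes | no |
| Thigh wasting, deformity, effusion, palpation pain | no | no | yes |

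Four of the five listed secondary objectives are absent from the longitudinal list. The inclusion examination records range of motion and thigh size ("Thigh circumference at 5, 10 and 15 cm from the base of the patella"). It does not mention effusion, deformity or palpation pain. Deformity appears elsewhere only as part of the radiographic grading. Secondary analysis nevertheless says that all these signs are collected at three visits.

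**3. What the named terms estimate.** Write the model as y_ij = μ + f(t_j) + b0_i + b1_i·t_j + e_ij for patient i at visit j. The expected value at a visit is then the same in both arms, and no parameter is a between-arm difference. With arm A_i (0 or 1) and categorical visit, y_ij = μ_j + δ_j·A_i + β·baseline_i + e_ij. Here δ_j is the arm difference at visit j, which is the quantity the secondary objectives ask for.

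**4. Why visit should be categorical (illustration only).** Training fills 6 of about 26 weeks. Suppose arm-by-time were added as a straight line. With t = 0, 6, 26, the slope of the arm difference d is [Σtd − (Σt)(Σd)/3] / [Σt² − (Σt)²/3], where the denominator is 712 − 1024/3 = 370.67. The true profiles below are assumptions. The 15 is borrowed from the sample-size section.

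| Assumed true difference at weeks 0, 6, 26 | Fitted at weeks 0, 6, 26 |
|---|---|
| 0, 15, 0 | 7.0, 5.9, 2.1 |
| 0, 15, 7.5 | 6.2, 6.9, 9.4 |
| 0, 15, 15 | 5.4, 8.0, 16.6 |
| 0, 10, 3 | 4.35, 4.34, 4.31 |

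In the last row the week-6 difference is understated by (10 − 4.34)/10 = 57%. If the baseline difference is forced to zero in that row, the slope is 138/712, and the fit is 1.16 at week 6 and 5.04 at week 26.

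**The case against.** The strongest reply is that the longitudinal paragraph was never meant to carry the comparison. Its stated purpose is progression, and the secondary endpoints have their own between-group tests. A reader might infer that the arms are never compared at 6 months. The documents do not support that: the two-sample tests apply to the secondary endpoints, and Objectives and endpoints sets a 6-month evaluation. What remains is that Secondary analysis does not state the 6-month contrast, and that those tests lie outside the longitudinal setting to which the missing-data methods belong.

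A second reply is that the quoted clause explains the random effects and is not a full list of fixed effects, that covariables are left open, and that an article may leave model terms to an analysis plan that is not shown. This has weight. But the article does name effects, variables and a post-hoc test, and exploring covariables does not prespecify a treatment contrast.

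Other stronger readings also fail:

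- **The model imposes a straight line and loses 57% of the effect.** The word linear does not appear, and a random slope does not stop the mean from being modelled by visit. The 57% needs both an assumed profile and an arm-by-linear-time term that the plan does not state.
- **ANOVA is invalid for the signs.** Their measurement scales are not given.
- **Tukey-Kramer compares only visits.** The text does not say which means are compared.
- **None of the listed variables is a secondary endpoint.** Mobility plausibly is range of knee motion.
- **The signs are recorded only at inclusion.** The heading names inclusion but does not exclude later visits, and the study-design figure is not shown.

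**Conclusion.** The point holds for the longitudinal model, not for the whole secondary analysis. As described, the model has no between-arm parameter and covers at most one of the five listed secondary objectives. The between-arm results at 6 months therefore rest on two-sample tests with no stated 6-month contrast and no tie to the missing-data methods. This is a should-fix.

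The size of any resulting error cannot be derived from the documents, because they give neither a 6-month loss rate nor an expected 6-month effect. The straight-line figures show only why visit should be categorical. The conclusion assumes that the named effects reflect the intended model. If the full analysis plan already has arm and arm-by-visit terms for these endpoints, only the wording and the list of variables need correcting.

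**What to change.** 1. For the continuous secondary endpoints in Objectives and endpoints, and for the secondary peak torques, specify a mixed model with arm, visit as a category, arm-by-visit and the baseline value. Report the between-arm difference with its confidence interval at 6 weeks and at 6 months.
2. Use this as the between-arm longitudinal analysis, in place of the repeated-measures ANOVA with Tukey-Kramer, and attach the planned missing-data sensitivity analysis to it.
3. If effusion, deformity or palpation pain is recorded as binary or graded, use a logistic or ordinal counterpart with the same arm-by-visit contrasts.
4. Reconcile Objectives and endpoints, Clinical examination at inclusion and Secondary analysis on which signs are measured at which visits.

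The cost is analysis-plan wording and, depending on the covariance structure chosen, a few more covariance parameters per endpoint. The continuous secondary endpoints need no new data. The sample size stays at 40 per arm and the primary analysis is unchanged.

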#### Method of accounting for missing, unused or invalid data

A sensitivity analysis of missing data will be performed to ensure the pertinence of the longitudinal data (MAR or MCAR). In order to assess the problem caused by missing longitudinal data at 6 months, estimation methods developed by Verbeke and Molenberg should be proposed [20,21].

## Discussion

In addition to being related to pain and a limitation in functional capacity, muscle weakness influences the progression of OA [7,22]. Severe levels of disability or inactivity induce muscle wasting and may contribute to the decline in strength reported in elderly people. These findings may have important implications for people with knee OA and knee pain, particularly in a therapeutic and preventative role of increasing muscle strength to reduce or stop disease progression. Scientific literature confirms that exercises, particularly strengthening exercises, are beneficial in terms of improved physical function and strength in people with knee osteoarthritis [23]. Yet, there is no scientific evidence for which type of strengthening exercises would have an impact on functional outcomes.

Isokinetic evaluation is used to quantify muscle strength, treatment and rehabilitation efficacy in case of mechanical [15] or neurological instability of the knee [24]. Moreover, isokinetic exercises can be used as personalized muscle strengthening techniques, offering a graduated and secure program with an objective measurement of the progress. Isokinetic exercises offer great selectivity for the motion required in ambulation and produce a faster rate of strength gain and reduced muscle tenderness than isotonic training [25]. Also, increases in heart rate and blood pressure seem to be lower with isokinetic compared to isometric exercises, which could be of particular importance among older patients with OA who often present comorbidities [11]. Interestingly, isokinetic eccentric exercises induce lower metabolic and cardiovascular responses than concentric exercises [26].

In accordance with the data in the literature, we expect to find an improvement of the quadriceps strength in the treated arm of the two groups after isokinetic strengthening. In case of superiority of the eccentric mode, the priority could be given to an eccentric training in the rehabilitation treatment of knee osteoarthritis patients.

